#### Plans to promote participant retention and complete follow-up {18b}

The research nurse will contact the participants to remember online scheduled sessions according to the protocol, as well as the online assessment battery comprising a set of validated self-report measures at each time point defined in the protocol.

The correct completion of all measures will be monitored by a research nurse.

#### Data management {19}

In this RCT, all data will be gathered online and recorded automatically. Data will be stored in a secure server, Reuma.pt, which works as an electronic clinical file available, designed to be used in real time while observing the patients. Patients have access to a dedicated and protected area where they can fill in the self-assessment questionnaires. Their answers are automatically loaded on the consultation page. Reuma.pt is registered with the national data protection authorities and respects all applicable ethical principles and the General Data Protection Regulation.

A specific protocol for MITIG.RA trial will be developed and protected by personal and non-transmissible username and password, limited to the research team and for the included patients.

The data entry screens will resemble the paper forms of the self-questionnaires included in the trial. Data integrity will be enforced through a variety of mechanisms. Referential data rules, valid values, and range checks are considered in the Reuma.pt. The option to choose a value from a list of valid codes and a description of what each code means is available where applicable. Additional errors, missing data, or inconsistencies will be detected by Reuma.pt, and a list of irregularities/per patient will be generated and shown to the research nurse whenever the patient profile is accessed in the platform.

After study completion, anonymized data will be made available for statistical analysis.

#### Confidentiality {27}

Subject confidentiality is strictly held by the participating researchers. All source records, including electronic ones, will be stored in secured systems. All data in Reuma.pt will be encrypted, anonymized, and made accessible only to the research team, through personal and untransmissible username and password.

No identifiable information concerning enrolled subjects will be released to an unauthorized third party. Subject confidentiality will be maintained across all submission and publishing stages.

#### Plans for collection, laboratory evaluation, and storage of biological specimens for genetic or molecular analysis in this trial/future use {33}

C-reactive protein (CRP) collection will be performed as part of the routine assessment and care of patients with RA, in order to determine disease activity status. No other biological specimens will be collected or stored in the scope of this trial.

## Statistical methods

### Statistical methods for primary and secondary outcomes {20a}

Descriptive analysis and test differences will be used to compare the baseline demographics and participants’ characteristics as well as variables of interest, such as participant’s dropout rates, reasons for dropout, and the presence/absence and severity of negative effects.

An intention-to-treat analysis will be conducted whenever possible and complemented with per-protocol analysis if needed.

Preliminary analyses will be conducted to guarantee that the necessary assumptions for the following tests are met. Analysis of covariance (ANCOVA) will be used to assess between-group differences in fatigue scores (the primary outcome) at the 3-month follow-up after the second booster session (32nd week), controlling for baseline values. The same analytic procedure will be used to examine the between-group differences in perceived disease activity, depression, mindfulness, and self-compassion (secondary outcomes) in the 32nd week. All effect sizes will be reported.

Additionally, time × group interaction effects on fatigue levels, perceived disease activity, depression, mindfulness, and self-compassion scores across the different time points will be tested via repeated measures analysis of variance (ANOVA), within-between interaction (with Bonferroni correction).

Potential predictors of treatment response (e.g. sociodemographic factors, baseline levels of fatigue, disease impact, depression, and anxiety) will be explored through regression analyses.

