### Trial design {8}

The MITIG.RA is a two-arm parallel superiority randomized controlled trial. Participants will be randomized (1:1) into one of two conditions: the experimental condition (MITIG.RA programme plus TAU) and the control condition (TAU only). The first version of the protocol was registered in ClinicalTrials.gov (NCT05389189) in May 2022, before the enrolment of patients. This protocol was written in accordance with the Standard Protocol Items: Recommendations for Interventional Trials (SPIRIT) guidelines. The Consolidated Standards of Reporting Trials (CONSORT) guidelines will be followed when reporting the results of the study.

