#### Implementation

A board-certified clinical psychologist with training in contextual approaches will implement the protocol, following the intervention manual. The facilitator will be provided with peer supervision during the implementation of the intervention. The intervention will be implemented in groups of 10 RA patients in 8 × 2 h weekly sessions, followed by 2 × 2 h Zoom booster sessions after 4 and 12 weeks post-intervention. The sessions will be held in private Zoom conferences, allowing the participants to interact and collaborate.

Each session will employ group dynamics, visual aids, comprehensive metaphors, complementary e-books, and experiential exercises. All sessions will follow the same general structure: they will open with a gentle grounding exercise, followed by a brief review of the proposed weekly assignment (feedback, difficulties, and comments on the practices). Then, the main session’s theme and underlying concepts are introduced, followed by the practice and sharing and discussion of the guided experiential exercises. The session closes up with a brief exercise.

The implementation and consolidation of learned strategies in daily routines and practices will be regularly encouraged and monitored. Supporting audio materials featuring guided exercises will be provided for this purpose. A logbook will be used for participants to register notes, homework, and exercises and to promote consciously driven and goal-oriented behaviour.

To be considered an ‘intervention receiver’, each participant will be required to have attended, at least, the first session of the intervention. Participants attending a minimum of 6 sessions will be considered completers. Reasons for drop-out will be assessed and registered whenever possible.

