#### Treatment as usual (TAU)

All participants will benefit from the usual standard care in accordance with the current practice at the participating centre, respecting international recommendations for the management of RA. Treatment as usual consists of regular appointments with the accompanying care team, mainly involving disease assessment, treatment adjustments, and lifestyle recommendations. The usual care may include, according to the caring physician’s orientation, treatment of comorbid conditions such as, for instance, depressive or insomnia-related symptoms with the use of antidepressants and benzodiazepines. All medications and adjunctive therapies will be registered at baseline and at each visit during the study period.

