#### Sample size {14}

The primary outcome of the study will be the difference in fatigue scores between the two intervention groups at week 32, controlling for baseline values. Based on the minimum clinical improvement established for RAID score and on our previous study assessing the responsiveness of RAID.7i, we expect a minimum difference in fatigue scores between the two groups of at least 3 points [54, 71, 72].

A sample size of 91 was indicated by G*Power for analysis of covariance (ANCOVA) [*α* = 0.05, 90% statistical power, effect size of 0.50]. Assuming a 30% attrition rate and rounding up for convenience, we plan to recruit a total of 120 participants (60 participants per arm).

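### MITIG.RA is given in therapy groups of 10, but the primary ANCOVA and the sample size treat patients as independent; if outcomes correlate within groups, the standard error is too small

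*Protocol article*

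**What the plan says.** All references are to the protocol article.

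- **Trial design {8}:** the patient is the unit of allocation. "Participants will be randomized (1:1) into one of two conditions".
- **Implementation (under Interventions):** "The intervention will be implemented in groups of 10 RA patients", over eight weekly two-hour sessions and two boosters, in video sessions "allowing the participants to interact and collaborate". Delivery is by one person: "A board-certified clinical psychologist with training in contextual approaches will implement the protocol".
- **Treatment as usual (TAU):** no groups are described. "Treatment as usual consists of regular appointments with the accompanying care team".
- **Statistical methods {20a}:** "Analysis of covariance (ANCOVA) will be used to assess between-group differences in fatigue scores (the primary outcome") at week 32, controlling for baseline. Secondary outcomes get the same model, and time-by-group effects go to a repeated-measures ANOVA. Test assumptions are to be checked beforehand, but no alternative is named if independence fails.
- **Sample size {14}:** "A sample size of 91 was indicated by G*Power for analysis of covariance (ANCOVA"), with inputs "0.05, 90% statistical power, effect size of 0.50". Recruitment is set at 60 per arm, allowing for 30% attrition.

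None of these sections mentions therapy group, an ICC, a random group effect, a robust variance or a design effect.

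**The concern.** This is a partially nested design: patients in one arm share a therapy group and patients in the other arm do not. The article treats group process as part of the treatment. Sessions rely on group dynamics and shared discussion, and the Discussion presents the group format as an active ingredient. Members of the same group may therefore end up more alike than members of different groups.

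Plain ANCOVA has no place for that shared variation. With a positive within-group correlation, the mean of the MITIG.RA arm is less precise than the model reports. The primary p-value is then too small, the confidence interval too narrow and the power overstated. The secondary ANCOVAs and the repeated-measures ANOVA share the fault.

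This is more than a detail left to an analysis plan, because the article names the primary model and sizes the trial on it, and both assume independent patients.

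**Working it through.** **The plan's own figure.** The stated 91 does not come out of a two-arm ANCOVA with one covariate, two-sided alpha 0.05 and 90% power. That calculation needs 45 patients if 0.50 is Cohen's f, and 171 if it is Cohen's d (f = 0.25). The 91 does appear with f = 0.50 and numerator df = 10, which does not fit a two-arm comparison. A d of 0.50 with an unstated baseline correlation near 0.7 also comes close (93 at 0.68, 88 at 0.70). That is a separate matter. What counts here is that no variant tried contains a design effect.

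**Inputs from the article.** Group size m = 10; 60 per arm, hence 60/10 = 6 groups; 30% attrition, hence 120 × 0.70 = 84 analysed, 42 per arm, or 7 per group if losses are even.

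**Assumed input.** ICC of baseline-adjusted week-32 fatigue within therapy group: 0, 0.02, 0.05, 0.10.

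**Formulas**, with equal arms and clustering in one arm only:

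- Design effect in the MITIG.RA arm: DEFF = 1 + (m − 1) × ICC
- Variance inflation of the arm difference: V = (1 + DEFF)/2
- True SE / reported SE: R = √V
- Two-sided type I error ≈ 2 × [1 − Φ(1.96/R)]

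Worked case, m = 10 and ICC = 0.05: DEFF = 1 + 9 × 0.05 = 1.45; V = 2.45/2 = 1.225; R = 1.107; 1.96/1.107 = 1.77; type I error ≈ 7.7%.

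| m | ICC | DEFF | R | Type I, formula | Type I, simulated |
|---|---|---|---|---|---|
| 10 | 0 | 1.00 | 1.000 | 5.0% | 5.0% |
| 10 | 0.02 | 1.18 | 1.044 | 6.1% | 5.9% |
| 10 | 0.05 | 1.45 | 1.107 | 7.7% | 7.6% |
| 10 | 0.10 | 1.90 | 1.204 | 10.4% | 10.3% |
| 7 | 0 | 1.00 | 1.000 | 5.0% | 5.1% |
| 7 | 0.02 | 1.12 | 1.030 | 5.7% | 5.8% |
| 7 | 0.05 | 1.30 | 1.072 | 6.8% | 6.8% |
| 7 | 0.10 | 1.60 | 1.140 | 8.6% | 8.5% |

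The simulated column fits the planned ANCOVA to 40,000 trials per row, with zero average effect and a baseline–outcome correlation of 0.5. A second simulation of 20,000 trials agreed to within half a percentage point (6.4% and 8.9% in the last two rows). Both return about 5% at ICC 0, so the excess comes from clustering.

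**Information left after attrition.** At ICC 0.05 and m = 7, V = (1 + 1.30)/2 = 1.15, so 84 analysed patients carry the information of 84/1.15 ≈ 73 independent ones. The 84 is already below the 91 that the plan says it needs.

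**What the remedy costs.** A model with a random group effect in one arm and Satterthwaite df was simulated with 6 groups of 7, without a covariate. At ICC 0 to 0.02 its type I error is about 4%, and it estimates the group variance as zero in 50 to 58% of trials. For an illustrative standardised effect of 0.6, power is 71 to 72% against 77 to 78% for the plain analysis at ICC 0. At ICC 0.05 it is 65 to 66% against 76%, but there the plain analysis is running at a type I error of about 6.8%.

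**The case against.** The strongest reply is that the ICC is unknown and may be small. The article supports part of this. A single psychologist follows a manual, so differences between therapists add nothing to between-group variance. The endpoint is one individual rating taken 24 weeks after the weekly sessions end and 12 weeks after the second booster. Nothing in the article supports the upper end of the range, 0.10, and at ICC 0.02 the excess is only about one percentage point.

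The type I figures also describe a particular null: an average effect of zero, with some groups gaining and others losing. If the programme and its groups change nobody's outcome, individual randomisation leaves no one-arm correlation and the ANCOVA stays near 5%.

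A reader might infer that the type I error of this trial does exceed 5%, or that the groups are closed. The documents support neither. They give no ICC, and they do not say whether membership is fixed. The figure of 6 groups is 60/10, not a planned number.

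What survives is the conditional point. For any positive within-group correlation the error runs in one direction. The general promise to check assumptions does not settle it: no fallback is named, and a test for clustering with about 6 groups has little power.

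**Conclusion.** The point holds in conditional form. The stated primary analysis and sample size ignore a grouping that the design creates in one arm. If week-32 fatigue correlates within therapy groups, the reported standard error is too small. At an assumed ICC of 0.05 the shortfall is about 7 to 11%, and type I error is about 6.5 to 7.6%, depending on attrition. At ICC 0 there is no error, and at 0.10 type I error is about 8.5 to 10%. If the treatment works but its effect varies by group, the practical consequence is a confidence interval that is too narrow and power that is overstated. These sizes rest on the assumed ICC, equal groups and even dropout. The change should be made, but the documents do not show that the primary result would be invalid without it.

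**What to change.** - Record therapy-group ID for every MITIG.RA patient.
- Pre-specify the primary week-32 analysis as a linear mixed model of fatigue on arm and baseline fatigue, with a random therapy-group effect in the MITIG.RA arm only (TAU patients as singletons) and Satterthwaite or Kenward-Roger df.
- Keep the plain ANCOVA as a sensitivity analysis.
- Carry the same group effect into the secondary and repeated-measures analyses.
- Restate the power over an assumed ICC range, for example 0 to 0.10, once the basis of the 91 has been clarified.

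**Cost.** One recorded variable and a few sentences; the Trial status section says no patient had been enrolled. Intervals will be wider. With about 6 groups, inference is slightly conservative and some power is lost when the ICC is near zero. Group ID exists in one arm only, so it can reveal allocation to the blinded analyst unless the code is fixed before data release. With one facilitator, therapist effects remain confounded with arm, and this model cannot remove them.

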### Data collection and management

#### Plans for assessment and collection of outcomes {18a}

The research team is responsible for the assessment and collection of outcomes, being the content and timing of the assessment similar to both intervention groups.

Clinical data and outcome measures will be collected online, via Reuma.pt (www.reuma.pt), the official and ethically approved national register of rheumatic patients.

Sociodemographic information will be collected from the patients’ files at baseline. Measurement of C-reactive protein levels and clinical examination and assessment of disease activity will be performed and registered at screening, baseline, and after 20 and 44 weeks by the rheumatologist. Medication monitoring and recording will be performed throughout the study, from screening to the last follow-up period.

At baseline, 8 weeks (post-intervention), 12 weeks (before the 1st booster session), and 20 weeks (before the 2nd booster session), participants will complete an online assessment battery comprising a set of validated self-report measures (see Fig. 1). This assessment will be repeated at 32 and 44 weeks to evaluate the persistence of potential therapeutic gains over time. Each patient will have private access to the questionnaires through a personal registered account. The research nurse will determine the correct completion of all measures. Those responsible for delivering the interventions will not be involved in any form of data collection and analysis over the duration of the trial.

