### Methods in analysis to handle protocol non-adherence and any statistical methods to handle missing data {20c}

Missing data analysis will be performed to determine the presence and level of randomness of missing data. Multiple imputation will be used to handle the missing data [73].

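### The supplementary repeated-measures ANOVA over six visits is a weak choice for the persistence question; a mixed model would use the same data better and give the arm difference at each visit

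*Protocol article*

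**What the plan says.** Under Statistical methods for primary and secondary outcomes {20a}, the primary analysis is a baseline-adjusted comparison at week 32: "Analysis of covariance (ANCOVA) will be used to assess between-group differences in fatigue scores (the primary outcome"). The same ANCOVA at week 32 is applied to the secondary outcomes. In addition, time × group effects on fatigue, perceived disease activity, depression, mindfulness and self-compassion are tested across the time points by "repeated measures analysis of variance (ANOVA), within-between interaction (with Bonferroni correction").

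The visits come from Plans for assessment and collection of outcomes {18a}: "At baseline, 8 weeks (post-intervention), 12 weeks (before the 1st booster session), and 20 weeks (before the 2nd booster session"), and then "This assessment will be repeated at 32 and 44 weeks", the last two in order to judge whether gains persist. The Discussion also says that repeated assessment will show the usefulness of the booster sessions and persistence up to six months.

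Three other statements bear on the point:
- Sample size {14} expects substantial loss: "Assuming a 30% attrition rate and rounding up for convenience".
- Section {20c} says "Multiple imputation will be used to handle the missing data", without exempting the longitudinal analysis.
- Section {20a} says "An intention-to-treat analysis will be conducted whenever possible and complemented with per-protocol analysis if needed", and also "Preliminary analyses will be conducted to guarantee that the necessary assumptions for the following tests are met".

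**The concern.** The ANCOVAs look only at week 32. The repeated-measures ANOVA is therefore the only stated comparison of the arms that uses weeks 8, 12, 20 and 44, and what the trial says about durability and booster sessions depends on it. Three features make it a poor tool for that.

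1. The univariate F test assumes sphericity. Correlation between fatigue scores probably falls as visits move apart, and here they are between 4 and 44 weeks apart. A correction protects the type I error but does not restore the power lost.
2. The sphericity-corrected univariate F has no direct pooled form under Rubin's rules, so it fits awkwardly with the planned imputation.
3. The interaction test has (6 − 1) × (2 − 1) = 5 degrees of freedom. It asks whether the two profiles differ in shape anywhere. It does not itself estimate the arm difference at week 44.

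At stake are the sensitivity and readability of the durability results, not the primary conclusion.

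**Working it through.** **Plan's own figure.** The protocol gives no power or sample size for this analysis. Its figure of 91 belongs to the week-32 ANCOVA and has no bearing here, so there is nothing to reproduce.

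**Inputs from the protocol.** 120 patients, 60 per arm. Assessments at weeks 0, 8, 12, 20, 32 and 44, with gaps of 8, 4, 8, 12 and 12 weeks. Attrition 30%, so about 120 × 0.7 = 84 patients with complete profiles if all attrition leaves a gap. Multiple imputation.

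**Assumptions not in the protocol.**
- Effect of 0.5 SD from week 20, and 0.4 SD at weeks 8 and 12.
- Monotone drop-out leaving about 70% complete, either completely at random (MCAR) or depending on the previous score (MAR).
- Two correlation structures: compound symmetry at 0.5, or decay of 0.7 per 12 weeks. Under decay the correlation is 0.7^(4/12) = 0.89 for visits 4 weeks apart and 0.7^(44/12) = 0.27 for visits 44 weeks apart.

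**Step 1: sphericity.** Greenhouse-Geisser epsilon is tr(V)² / [5 × tr(V²)], where V is the doubly centred covariance matrix of the six visits. It is 1.0 under compound symmetry and 0.57 under the decaying correlation. In the second case the 5 numerator df shrink to an effective 5 × 0.57 ≈ 2.9.

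**Step 2: power for the same time × group hypothesis after drop-out.** The simulations used 1,000 trials per scenario, 15 imputations and two-sided 5%. The mixed model had unstructured covariance and was fitted by maximum likelihood.

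| Correlation | Drop-out | Imputation + univariate RM-ANOVA | Mixed model | Gap (points) |
|---|---|---|---|---|
| Compound symmetry 0.5 | MCAR | 56.2% | 60.9% | 4.7 |
| Compound symmetry 0.5 | MAR | 58.4% | 63.4% | 5.0 |
| Decay 0.7 per 12 weeks | MCAR | 50.9% | 73.8% | 22.9 |

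The decaying-correlation MAR case was not obtained for the univariate test. With no true effect (MCAR), the rejection rates were 4.8% (ANOVA) and 5.2% (mixed model) under compound symmetry, and 3.8% and 3.4% under decay. The mixed model's advantage is therefore not bought with excess type I error. The Monte Carlo standard error of one power figure is √(0.5 × 0.5 / 1000) = 1.6 points.

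**Step 3: a multivariate repeated-measures test on the imputed data** (separate runs, 900 trials per scenario).

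| Correlation | Drop-out | Imputation + multivariate test | Mixed model | Gap (points) |
|---|---|---|---|---|
| Compound symmetry | MCAR | 61.2% | 61.1% | −0.1 |
| Compound symmetry | MAR | 60.6% | 62.3% | 1.7 |
| Decay | MCAR | 71.9% | 74.6% | 2.7 |
| Decay | MAR | 72.7% | 75.6% | 2.9 |

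**Step 4: where the large gap comes from.** With complete data and decaying correlation, the univariate test had 63 to 66% power against 79% for the multivariate test. With complete data and compound symmetry, the univariate test was slightly better (73.6% against 71.1%, MCAR runs). The large loss is thus due mainly to non-sphericity rather than to missing patients.

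**Limit of the check.** These runs compare tests of the interaction across all six visits. The model proposed below, with baseline as a covariate and outcomes from week 8, was not itself simulated.

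**The case against.** A reader might infer that the analysis discards everyone without a full set of six assessments and so rests on the roughly 70% who complete. The protocol does not support this. Section {20c} plans multiple imputation, {20a} plans intention-to-treat where possible, and nothing describes a complete-case analysis. A completer-only ANOVA would lose about 10 points (compound symmetry) to about 28 points (decay) of interaction power against the mixed model, but it is not what is planned. It would also be unfair to set the power of the 5-df interaction beside that of a single week-32 contrast. These are different hypotheses, and the week-32 contrast is already covered by the ANCOVA.

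Other parts of the defence also stand. Unequal spacing is no error in itself, because ANOVA treats time as a category; it matters only through sphericity. The planned assumption checks could lead to a correction. Pooled multi-parameter tests exist, so imputation does not rule out testing the interaction. The Bonferroni remark plausibly points to follow-up comparisons, which might include arm differences by visit. Pooling rules and the choice of correction are details that an article may leave to an analysis plan, so their absence is not held against it.

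What the defence does not remove is the stated choice of method. A sphericity correction leaves the power loss in place; the ANOVA figures above already use one. The Bonferroni remark names neither the contrasts nor any estimate by visit. The multivariate test that would nearly close the gap is not mentioned.

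**Conclusion.** The point holds as a modest one about a supplementary analysis. The protocol fixes a univariate method that is doubtful for this visit schedule, awkward to combine with its own imputation, and not aimed at the quantity that the persistence claims need.

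The cost in power depends on correlations that the protocol does not give. It is about 5 points if compound symmetry holds and about 23 points if correlation decays by 0.7 per 12 weeks, the latter under MCAR drop-out only. It is 0 to 3 points if a multivariate test is used on the imputed data. Decay seems the more plausible pattern over 44 weeks, but that is a judgement. The primary ANCOVA and the sample size are not affected.

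**What to change.** In {20a}, replace the repeated-measures ANOVA by a linear mixed model for repeated measures:
- **Outcomes:** weeks 8, 12, 20, 32 and 44.
- **Fixed effects:** baseline score, HADS stratum (the randomisation factor), arm, visit and arm × visit.
- **Estimation:** unstructured covariance with a small-sample degrees-of-freedom correction.
- **Population:** all randomised patients with any post-baseline value.
- **Reporting:** the arm difference with its confidence interval at each visit, week 44 included.

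Keep the week-32 ANCOVA as the primary analysis.

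The cost is a change of wording and a standard procedure, and the Trial status section says that no patient had been enrolled. The one drawback is that an unstructured covariance over five visits may fail to converge, so a fallback structure must be named in advance.

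### Bonferroni in the additional time × group analyses is valid, but Holm gives the same family-wise control and never rejects less, so a modest amount of power in those tests is given up

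*Protocol article*

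**What the plan says.** Statistical methods for primary and secondary outcomes {20a} describes two layers of analysis.

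- **Week-32 ANCOVAs.** Fatigue, the primary outcome, is compared between arms at week 32, adjusted for baseline. For the rest, "The same analytic procedure will be used to examine the between-group differences in perceived disease activity, depression, mindfulness, and self-compassion (secondary outcomes") at the same week. No multiplicity correction is attached to either.
- **Longitudinal analyses.** These are introduced by "Additionally, time × group interaction effects on fatigue levels" and cover "time × group interaction effects on fatigue levels, perceived disease activity, depression, mindfulness, and self-compassion scores across the different time points". The method is repeated-measures ANOVA, "within-between interaction (with Bonferroni correction").

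The second layer lists five outcomes, one of which is the primary outcome. The section does not say whether the correction runs over the five outcomes, over comparisons between visits after each ANOVA, or over both. It gives no adjusted significance level. The sample size section plans power for the ANCOVA only.

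**The concern.** Bonferroni compares every p-value in a family of m tests with α/m. Holm orders the p-values and compares the smallest with α/m, the next with α/(m−1), and so on up to α, stopping at the first failure. Both control the family-wise error strongly whatever the dependence between tests. Holm's first threshold equals Bonferroni's and its later ones are larger, so Holm can add rejections and cannot lose any. For any family of two or more tests, Bonferroni is therefore the less efficient choice at the same error guarantee.

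This matters here because the Discussion part of the abstract expects fatigue, perceived impact, emotional distress and emotion regulation to improve together. Several true effects in one family is the situation in which Holm gains most. At stake is how many of the longitudinal effects can be declared, not the primary conclusion.

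**Working it through.** **Plan's own figure.** There is none for these tests: no power, family size or adjusted level is given. The 91 in "A sample size of 91 was indicated by G*Power for analysis of covariance (ANCOVA") belongs to the week-32 comparison and is not used below.

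**Inputs**

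- Patients per arm: "Assuming a 30% attrition rate and rounding up for convenience, we plan to recruit a total of 120 participants (60 participants per arm"). Hence 60 × (1 − 0.30) = 42 per arm, 84 in total.
- Family: m = 5 outcomes as listed. This is one reading of the sentence, not something it states.
- Family-wise α = 0.05, two-sided (assumed for this family).
- True effect: 0.5 or 0.6 SD (assumed).
- Correlation between test statistics: 0.5 (assumed).

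**Thresholds for m = 5**

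- Bonferroni: 0.05/5 = 0.0100 for every test.
- Holm: 0.05/5, 0.05/4, 0.05/3, 0.05/2, 0.05/1 = 0.0100, 0.0125, 0.0167, 0.0250, 0.0500.

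**Bonferroni and uncorrected power per outcome, by formula.** Each test is represented by a z-statistic with mean d × √(n/2).

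- d = 0.5: 0.5 × √21 = 2.29. Against the critical value 2.576 (level 0.01), power is Φ(2.29 − 2.576) ≈ 39%. Against 1.960 (level 0.05), it is Φ(2.29 − 1.960) ≈ 63%.
- d = 0.6: 0.6 × √21 = 2.75. Power is about 57% at level 0.01 and about 78.5% at level 0.05.

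**Holm, by simulation** (400,000 sets of five equicorrelated z-statistics per scenario, correlation 0.5). Average power per truly affected outcome:

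| True effects | Effect | Bonferroni | Holm | Gain (points) |
|---|---|---|---|---|
| 1 of 5 | 0.5 SD | 39% | 39% | about 0 |
| 2 of 5 | 0.5 SD | 39% | 40% | about 1 |
| 3 of 5 | 0.5 SD | 39% | 42% | about 3 |
| 5 of 5 | 0.5 SD | 39% | 47% | about 8 |
| 5 of 5 | 0.6 SD | 57% | 67% | about 10 |

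**Checks**

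- In every simulated set, Holm rejected every hypothesis that Bonferroni rejected.
- The chance of at least one rejection is identical, because the first threshold is the same: about 74% for both with all five real at 0.5 SD.
- With all five real at 0.5 SD, the chance of declaring all five rises from about 9% to 25%.
- With all five null, the family-wise error is the same for both: 0.049 at correlation 0 and 0.041 at correlation 0.5.
- Correlation does not drive the gain. With all five real at 0.6 SD it is about 11 points at correlation 0, 10 at 0.5 and 8.5 at 0.8. The number of true effects drives it.

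**If the family is visit contrasts instead.** There are six assessments (baseline and weeks 8, 12, 20, 32 and 44), hence 6 × 5/2 = 15 possible pairs of visits. Bonferroni would test all 15 at 0.05/15 = 0.0033, and Holm would start at 0.0033 and relax. Holm again cannot reject less, but the percentages in the table do not apply.

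**The case against.** **This is a preference, not a defect.** Bonferroni inflates no error and contradicts nothing in the plan. That stands, and the point is offered only as a better method at the same guarantee.

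**A reader might infer that power for the secondary outcomes in general is lost.** The article does not support this. Its secondary outcomes are tested first by week-32 ANCOVA without a stated correction, and those tests lose nothing. The corrected tests are additional and include fatigue, the primary outcome.

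**A reader might also infer that the text should read Holm across the five outcomes.** The article does not support that either. The correction is named beside the within-between interaction and may cover only comparisons between visits. The five interaction tests would then each run at 0.05, and a Holm step across outcomes would be a new correction. In the illustration, power per outcome would fall from 63% to 47% at 0.5 SD and from 78.5% to 67% at 0.6 SD. This objection stands and limits what the fix may say.

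**The size rests on a stand-in.** The planned interaction tests are F tests over up to six assessments, with several numerator degrees of freedom; the illustration uses one-degree-of-freedom z-tests with assumed effects. In addition, 42 per arm is the number of completers, whereas the plan foresees intention-to-treat analysis where possible and multiple imputation. This stands against the exact percentages, not against the direction.

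**Bonferroni yields simple simultaneous confidence intervals and Holm does not.** This stands and is a legitimate reason to keep Bonferroni, especially for visit contrasts.

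**Conclusion.** The concern holds in a narrow form. Whichever family was intended, Holm would control the same family-wise error and reject at least as much, so Bonferroni gives up some power in the additional longitudinal tests. If the family is the five outcomes, the illustrative gain in power per outcome runs from about 0 points (one real effect) to about 8 to 10 points (all five real at 0.5 to 0.6 SD). That range assumes 42 per arm, correlation 0.5 and z-tests in place of the interaction F tests. The upper end needs all five effects to be real. The primary analysis, its α and the sample size are untouched. This is a minor, optional efficiency gain.

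**What to change.** In Statistical methods {20a}, replace *with Bonferroni correction* by *with Holm correction*, applied to the same family that Bonferroni was meant to cover, and name that family: the outcomes, or the post hoc visit contrasts. If no correction across the five outcomes was intended, do not add one.

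Report Holm-adjusted p-values. Label the accompanying 95% confidence intervals as unadjusted, because such an interval can exclude zero while the adjusted p-value exceeds 0.05.

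The cost is one word in the text and one line of code, plus the loss of simple simultaneous intervals that match the tests. The trial status section reports that no patient had been enrolled, so at that stage the change could be made before any data were seen.
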